**Criteria for discontinuing or modifying allocated interventions {11b}**

All adverse events will be treated on a case-by-case basis. In the event of an unanticipated adverse event that may cause direct harm or threat to the participants or others that are related to study implementation, the local JHCP staff will notify the PI. An unanticipated event report will be submitted promptly to the Cameroon National Ethics Committee and the UCL ethics committee per protocol.

**Strategies to improve adherence to interventions {11c}**

The main strategies employed to encourage participant adherence to the intervention is to ensure that participants and their economic dependents have the best possible experience whilst accessing care at the hospital and to reduce the barriers to access to care. A key concern is that participants or their nominated economic dependents will not go to the hospital to seek care when sick because they face large barriers to access e.g., lack of understanding of illness, distrust in healthcare or not having enough money to get to the hospital. Treatment participants receive information at randomisation, midline and endline regarding what is provided as part of the health insurance product, how to access it and whom to contact if they are having difficulties. Data is collected during the midline and endline survey regarding the participant's experience of using the health insurance product. If the participant has not used the insurance product because they forgot they are part of the treatment group the participant is reminded of the health insurance product and encouraged to use the intervention if needed by the enumerator and the site supervisor at the end of the survey. If the participant has had a bad experience whilst accessing care at the hospital, this is reported to the site supervisor and to the research staff. This problem will be discussed whilst the participant is being surveyed by the enumerator. At the end of the survey, the site supervisor will discuss their experience with the participant and ensure that any issues will be resolved and encourage them to use their health insurance product if needed. Experienced POWER enumerators are based at the hospital throughout the intervention period to support the patients throughout their clinical pathway. If there are any issues with treatment or access to care, the POWER staff report it directly to the research team for a resolution. The CBOs and specifically peer leaders and mobilisers support the adherence of participants to the intervention by keeping in regular contact with the participants throughout the lifetime of the project. Regular contact allows participants with concerns regarding the project or the intervention specifically the opportunity to speak up. Any problems are communicated to the research team and resolved. All resolutions are discussed with the participants. Peer leaders and mobilisers use their strong relationships with the participants and their status in this vulnerable population to engage participants and encourage adherence to the intervention.

**Relevant concomitant care permitted or prohibited during the trial {11d}**

There are no restrictions on concomitant care.

**Provisions for post-trial care {30}**

Any participants who suffer harm, e.g., psychological distress, as a consequence of the POWER project will be supported by the relevant CBO's psychological support services. Those in the control group, that remain in the study until the end of the project, will receive the same health insurance product for themselves and their economic dependents for 12 months.

**Outcomes {12}**

**Overview**

There are several methods of data collection. The socio-economic and biobehavioural surveys occur over three time periods: baseline, 6 months after baseline (midline), and 12 months after baseline (endline). The SMS survey occurs fortnightly, commencing just after the completion of the baseline for 52 weeks. The surveys are administered in both French and English, depending on the participant's language preference.

**Primary outcome measure**

Measured using questionnaires developed by the study team where not otherwise stated at 1, 6 and 12 months:

1. STI acquisition measured using % test positive for syphilis, % test positive for chlamydia, % test positive for gonorrhoea. STI symptoms prevalence measured using % who had any symptoms of STI in the last 30 days: vaginal discharge, lower abdominal pain outside of diarrhoea or menstrual period, wound or ulcer on genitals, burns during urination, swelling in the groin, itching in the genital area, pain during the sexual act, bleeding outside of period

2. HIV status measured using % testing HIV positive

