There are several reasons why economic shocks may lead to STIs and HIV acquisition. The main reason lies in the fact that the low access to formal well-paid jobs and productive assets makes women in Africa prone to use commercial and transactional sex as risk-coping strategies. Such strategies may be attractive given that they allow women to raise money quickly and they can earn up to three times more compared to other occupations (11). Relationships developed with men through commercial and transactional sex can also result in other financial or in-kind gifts, which could also help women to cope with economic shocks (12). Women who engage in commercial and transactional sex are incentivised to provide unprotected sex because men are generally willing to pay more for unprotected sex. It is estimated that sex workers can earn 9% more in Kenya and 66% more in India (11) for an unprotected sex act. In addition to unprotected sex, commercial and transactional sex are risky practices because they often lead to multiple, concurrent sexual partners and partners at greater risk of HIV infection (older men and sex workers’ clients). In addition to increasing risky behaviours, economic shocks may also lead to STI and HIV infection if households cut health expenditures concerning STI treatment and HIV prevention services.

Determining whether an economic shock is the missing piece of the HIV puzzle is critical as economic shocks are very common in Africa and these women often lack risk-coping strategies. Economic shocks are a key issue for many African households. At least 60% of African households report large and sudden losses in income every year (13) but only 10% of the poorest households in Africa benefit from social safety net programs to negate income fluctuations (14). Among the shocks experienced by households, health shocks are of particular concern given that they are more frequent, more costly and more concentrated among the poor than other economic shocks (15). If women adopt risky sexual behaviours to cope with negative economic shocks providing women with formal risk-coping strategies could be a very promising approach to preventing HIV. However, no previous study has been designed to specifically answer this research question. Hence, there remain important gaps in understanding.

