**Intervention description {11a}**

The insurance product, provided by GMC Insurance, covers the participant and up to six of their (nominated) economic dependents and is offered for 12 months. An economic dependent is anyone that depends on the participant financially for health care and can include family members, friends and sex work intermediaries (e.g., pimp). The health insurance product provides free health coverage, there are no out-of-pocket costs, with a cumulative ceiling for each group (the participant and their economic dependents) of 500 000 FCFA (= 638,55 GBP, in 2022 prices) following an illness or an accident and is only valid at the Cité Verte Hospital, Yaoundé, Cameroon. The negotiated ceiling of 500 000 FCFA provides good coverage of health expenses for 12 months in Cameroon. If the sum of 500,000 FCFA has been reached (by the participant and their economic dependents combined), participants must pay for the health expenses themselves. Before the group reaches the 500 000 FCFA limit, the participant will be notified to ensure that they are informed when consuming health care. Costs covered by the insurance product are: consultation fees; pharmaceutical fees; medical fees and; hospitalization fees for non-chronic pathologies. Costs not covered by the insurance product are: chronic diseases (e.g. diabetes, high blood pressure, asthma, sickle cell anaemia, obesity...); maternal health care (prenatal care, delivery, postnatal care); illness resulting from civil or foreign war, civil commotion or riot; injury following a violent quarrel except in cases of self-defence; epidemics declared as such by a competent authority (e.g. COVID-19); cosmetic care; dietary care; weight loss or rejuvenation; sterility or abortion treatment; psychiatric treatment; alcoholism; dialysis; dental care and; ophthalmologic care.

The insurance product was rolled out on the 15^th^ of November 2021 and ended on the 14^th^ of November 2022.

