**Sample size {14}**

The baseline study has recruited 1,508 unmarried girls and young women engaging in transactional (753) and commercial (755) sex in Yaoundé, Cameroon. Currently, 1,147 participants have been randomised via participatory randomisation, 568 participants allocated to the control arm and 579 allocated to the treatment arm. To maximise statistical power, STI-positive participants receive free treatment at baseline to start the trial with an STI-free cohort. Participants will also receive free treatment at midline to allow for the possibility to observe more than one STI per participant over the trial period. Free treatment will also be provided at endline for ethical reasons. Assuming that 20% of participants will get at least one STI over the trial period, this sample size is sufficient to show a decrease of 30% (6 percentage points) in the incidence of any STI in the treatment group assuming 80% power and a significance level of 5%. To conduct analysis separately among the sub-samples of those engaging in commercial and transactional sex, the MDE is a ~40% reduction (8.3 percentage points) in STI incidence. Assuming an HIV incidence of 4% over the trial period, the sample size would allow the detection of a decrease of 65% in HIV incidence (2.6 percentage points).

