**Statistical methods**

**Statistical methods for primary and secondary outcomes {20a}**

All statistical analyses will be conducted using STATA. Descriptive statistics will first be used to summarise participant characteristics between the study groups. To investigate the effect of health insurance on primary and secondary outcomes, the analysis will use an intention-to-treat (ITT) approach where participants will be analysed in their allocated randomised study group. If there are non-compliers, i.e., participants and economic dependents who do not use the health insurance product when sick, we will also estimate the local average treatment effect (LATE). To investigate the effect of health insurance on primary and secondary outcomes, baseline characteristics will be compared for the treatment and control groups and determine whether there is differential attrition between the two groups. Outcomes for the treatment versus the control group will then be compared accounting for any baseline or attrition differences using ordinary least squared. The analysis will be conducted for all women and then separately for women engaging in transactional and commercial sex separately. A causal mediation analysis will be conducted to assess how much of the effect of health insurance on STI and HIV acquisition operates through risky sexual behaviours.

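### The primary STI outcome is called acquisition but counts only new infections still present at the test, so earlier treatment in the insured arm could pass for prevention

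*Protocol*

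**What the plan says.** Protocol, Primary outcome measure: the outcome is "STI acquisition measured using % test positive for syphilis", with the same percentage for chlamydia and gonorrhoea. Overview puts the surveys at baseline, 6 months and 12 months, and section {18a} has the biological tests done at the same visits. Section {18a} adds that only active syphilis counts at midline and endline, and that midline tests HIV and just the two most prevalent STIs.

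Sample size {14} treats the outcome as cumulative: "Assuming that 20% of participants will get at least one STI over the trial period". It calls the sample "sufficient to show a decrease of 30% (6 percentage points) in the incidence of any STI in the treatment group". It also provides free STI treatment at baseline, so that the cohort starts free of STIs, and again at midline.

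Intervention description {11a}: "Costs covered by the insurance product are: consultation fees; pharmaceutical fees; medical fees and; hospitalization fees for non-chronic pathologies". The exclusions that follow do not mention STIs. Section {6b} says controls receive nothing. Section {18b} offers free treatment in both arms after a positive study test, paid by the project and not by the insurance.

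Background and rationale {6a} says that "economic shocks may also lead to STI and HIV infection if households cut health expenditures concerning STI treatment and HIV prevention services". Section {20a} plans a mediation analysis of "how much of the effect of health insurance on STI and HIV acquisition operates through risky sexual behaviours".

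**The concern.** Acquisition and incidence count every new infection. A positive test at a visit counts only those that have not cleared by then. If clearance between visits were the same in both arms, the measure would under-count equally and the relative comparison would survive. Here the intervention itself may change clearance, because it removes the cost of consultations and medicines in one arm only.

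The research hypothesis is that insurance reduces risky sex and so prevents infection. Under the present labels, a lower positive rate in the insured arm would be reported as infections prevented, although some or all of it could be infections treated sooner. The Protocol has no rule for counting an STI that is diagnosed and treated between visits. Its one related analysis, in section {20c}, concerns infections left untreated at baseline. The 30-day symptom measure in the same primary outcome is open to the same problem.

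**Working it through.** **1. What a follow-up positive represents.**
- Infections found at baseline are treated, and those found at midline are treated again ({14}).
- A later positive is therefore meant to be an infection acquired since the last visit at which it was tested and treated, and still present at the test.
- An infection acquired and cured between two visits is counted nowhere.
- For an STI not tested at midline ({18a}), the uncounted interval runs from baseline to endline.

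**2. Where the arms differ.**

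| Source of STI care | Treatment arm | Control arm |
|---|---|---|
| Paid by the study after a positive study test ({14}, {18b}) | yes | yes |
| Insured consultation and medicines between visits ({11a}) | apparently yes | no |
| Care obtained elsewhere ({11d}, no restriction) | possible | possible |

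Only the second row differs by design.

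**3. The Protocol's own figure.** A 30% decrease from 20% is 0.20 × 0.30 = 0.06, so 14% v 20%. With a pooled-variance normal test, two-sided 5% (sidedness is not stated, so this is assumed) and 80% power, this needs 615 women per arm. With the 568 control and 579 treatment women randomised, power is 77.3% and the detectable difference is 6.2 points. The stated 6 points is thus met only after rounding. That small gap does not bear on this point.

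**4. Illustration.** Let A be the share of women acquiring an STI, equal in both arms, and c the share of those women whose infection has cleared by the test.

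Positivity = A × (1 − c).

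Take A = 0.20, c = 0 in controls and c = e in the insured arm. The difference is then 0.20 × e. The values of e are assumptions; the Protocol gives none. The last column is the chance of a significant result favouring insurance at 568 v 579, if every randomised woman is tested.

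| e | Insured arm | Control arm | Difference | Chance of significance |
|---|---|---|---|---|
| 0% | 20% | 20% | 0 points | 0.025 |
| 10% | 18% | 20% | 2 points | 0.14 |
| 20% | 16% | 20% | 4 points | 0.42 |
| 30% | 14% | 20% | 6 points | 0.77 |

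Some clearance in controls does not remove the effect. If 25% acquire an STI in each arm, and 20% of control and 40% of insured infections clear, positivity is 0.25 × 0.80 = 20% v 0.25 × 0.60 = 15%. That is a 5-point difference, significant with probability 0.61.

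**5. Unit.** Here e is the share of positive women removed, not of infections. A woman with more than one infection leaves the count only if all of them clear. If each infection has the same chance of clearing, clearing 30% of infections removes at most 30% of positive women.

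**The case against.** Several counter-arguments are good, and most of them stand.

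- **The measure is not ordinary prevalence.** A reader might infer that it is plain point prevalence. The treatment at baseline and midline, and the analysis in {20c} that removes women whose baseline infection went untreated, show that it targets new infection. It is an under-count of new infections, and the point is put that way here.
- **The mediation analysis is not blind to the problem.** A reader might infer that it cannot separate treatment from behaviour. The wording in {20a} allows for effects outside risky sexual behaviour, and an effect of treatment alone would fall there. Risky behaviour, treatment-seeking when sick and health care utilisation are also measured, and HIV is a second primary outcome that treatment does not clear.
- **Insured STI care is inferred.** It follows from the cover and exclusion lists in {11a}; no section states it.
- **Uptake may be low.** Care is limited to one hospital, with card and photo ID. Section {11c} treats non-attendance as a key concern, and the Discussion warns of under-use. Excess clearance could be near zero.
- **Questionnaire items are not shown.** Section {18a} says that the survey covers demand for healthcare, so suitable items may already exist.

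None of this repairs the label. The outcome and power statements still say acquisition and incidence for a measure that omits infections cured between visits, and the Protocol itself names spending on STI treatment as a pathway.

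**Conclusion.** The point holds as one of definition and interpretation. The STI outcome measures new infection since the last treated visit that is still detectable at the study visit. A difference between arms on it cannot by itself be called infections prevented.

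The size is unknown. Differences of 0 to 6 points follow from assumed excess removal of 0% to 30% of positive women, with 20% acquisition in each arm. The 30% figure is simply the one that reproduces the design effect and is not a forecast. The conclusion also assumes that the insurance pays for STI care.

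A reader might go further and call the primary analysis invalid. The Protocol does not support that: the contrast in positivity is a valid intention-to-treat effect, shorter infection is a real benefit, and the HIV outcome is not affected.

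**What to change.** 1. In Primary outcome measure and Sample size {14}, restate the STI outcome as new infection since the last treated visit, still detectable at the study visit. State that a difference on this outcome alone will not be reported as infections prevented.
2. Add a sensitivity endpoint: a woman counts as infected if she tests positive or reports an STI diagnosed or treated since her last visit. Use the same survey items in both arms, and existing care-seeking items where endline is already done. Use hospital records, which cover insured care in one arm only, purely as a check.
3. Present the two versions as sensitivity analyses with opposite likely biases. The test-only version may favour insurance through earlier treatment; the added version may count against it through more diagnosis. They are not bounds, since recall and under-reporting could put the truth outside both.
4. In {20a}, state that the part of the effect not operating through risky sexual behaviour may include earlier treatment.

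The cost is rewording, one or two survey items and one extra analysis; treatment, visits and allocation do not change. The downsides are reliance on self-report, possible over-diagnosis in the insured arm, and partial coverage. Insurance ended on 14 November 2022 and this version is dated 10 March 2023, with follow-up still open, so few endline interviews may remain.

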**Secondary outcome measures**

Secondary outcomes include:

1. Physical health of participants measured using % of participants with good health, % of participants with a chronic illness other than Hepatitis B, the average number of chronic illnesses, % of participants who were sick in the last 30 days, % who sought treatment from a qualified health worker if sick in the last 30 days, % of participants with abnormal levels of Gardnerella vaginalis (GV), Mobiluncus, Candida and streptococcal in the vagina (only at endline)

2. Physical health of economic dependents measured using % of economic dependents with good health, % of economic dependents with a chronic illness, the average number of chronic illnesses per economic dependent, % economic dependents who were sick in the last 30 days, % economic dependent who were sick during sex act with last client, % economic dependents who were sick during sex act with the penultimate client, % of children with good health

3. Beliefs regarding control over own health measured using % who believe that nothing can be done to prevent illness, % who believe that being in good health is a matter of luck

4. Poverty measured using total expenditures, asset index, income from sex work, amount of savings, % who have Informal shock-coping strategies, average amount of transfers received and sent, % who have a debt, amount of the debt, food insecurity

5. Education/training measured using % school dropout, new enrolment in schools, % who are undertaking professional training

6. Other occupation measured using transitions out of sex work, % who have other occupation, share of sex work income in total income

7. Risky sexual behaviours measured using % of condom use with last and penultimate client using a double list experiment and the colourbox method, a newly indirect elicitation method developed by the team members, number of clients per week, type of sex acts performed with last client, self-reported risk preferences with sex (out of 10 scale), % of were pregnant the last 6 months, % who performed both transactional sex and sex work

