**Data collection and management**

**Plans for assessment and collection of outcomes {18a}**

There are several methods of data collection. The socio-economic and biobehavioural surveys occur over three time periods: baseline, 6 months after baseline (midline), and 12 months after baseline (endline). The surveys are administered in both French and English, depending on the participant's language preference. The primary outcomes of the study are STI acquisition and HIV status will be measured via the biobehavioural and socioeconomic survey conducted at baseline, midline and endline. At baseline, we will test for syphilis, chlamydia, gonorrhoea and trichomoniasis. For financial reasons, we will only collect HIV and the two most prevalent STIs at the midline. At endline we will test for all the STIs tested at baseline (syphilis, chlamydia, gonorrhoea and trichomoniasis). In addition, to allow for a better understanding of the participants' non-sexually transmitted infections status, the levels of GV, Mobiluncus, Candida and streptococcal in the vagina will also be tested. Testing the levels of these bacteria and fungi is a secondary outcome. It is important as sexual activity is associated with an increased risk of imbalance of these bacteria or fungi in the vagina which may lead to infections such as Bacterial vaginosis (BV), Candidiasis and Group B Strep infection. Evidence suggests that there is a positive relationship between a person having these infections and an STI and HIV(17). Biological tests (blood tests and vaginal swabs) to test for STIs, HIV and non-sexually transmitted bacteria and fungi are conducted at the same time as the socioeconomic survey.

Other secondary outcomes are measured via the biobehavioural and socioeconomic survey conducted at baseline, midline and endline. Additional measures for secondary outcomes will also be captured in the fortnightly SMS survey. The survey questionnaire will include sociodemographic questions, income, health status, demand for healthcare, economic shocks, STI prevention, risky sexual behaviours, violence, personality traits and preferences.

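### A primary STI measure counts self-reported symptoms with no positive test, so free care for non-STI conditions in the insured arm can move it without any change in STI acquisition

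*Protocol*

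**What the plan says.** The protocol's Primary outcome measure section opens item 1 with three test-based percentages: "STI acquisition measured using % test positive for syphilis, % test positive for chlamydia, % test positive for gonorrhoea". The same item then adds a questionnaire measure: "STI symptoms prevalence measured using % who had any symptoms of STI in the last 30 days: vaginal discharge, lower abdominal pain". The list continues with genital ulcer, burning on urination and groin swelling, and ends with "itching in the genital area, pain during the sexual act, bleeding outside of period". That makes eight complaints, any one of which scores an event. No rule ties the answer to a test result.

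Four other places bear on it:

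- **Plans for assessment and collection of outcomes {18a}** describes imbalances of vaginal organisms "which may lead to infections such as Bacterial vaginosis (BV), Candidiasis and Group B Strep infection". It groups these under non-sexually transmitted infections. The matching outcome, "of participants with abnormal levels of Gardnerella vaginalis (GV), Mobiluncus, Candida and streptococcal in the vagina (only at endline"), is secondary.
- **Intervention description {11a}**: "Costs covered by the insurance product are: consultation fees; pharmaceutical fees; medical fees", plus hospital fees for non-chronic conditions. Genital and urinary infections are not among the listed exclusions.
- **Plans to promote participant retention {18b}** offers free treatment of a positive STI test in both arms, paid by the project and not by the insurance.
- **Who will be blinded {17a}** leaves participants unblinded.

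**The concern.** The trial's hypothesis is that insurance reduces risky sex and so prevents STIs and HIV. A primary measure should respond to that pathway. This one also responds to another: an insured woman has her thrush or urinary infection treated and stops reporting itching or burning. Because study-detected STIs are treated free in both arms, much of the difference in care between arms falls on other conditions, although insured care between visits may also treat some STIs. Unblinded self-report adds a further route that has nothing to do with infection.

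At stake is the reading of the result. A lower symptom percentage in the insured arm would stand among the primary STI outcomes and could be taken as evidence of STI prevention when acquisition had not changed. Conversely, a real STI effect would be diluted by background symptoms.

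**Working it through.** **Inputs from the protocol (Sample size {14}).** 20% of participants with at least one STI over the trial, a 6-point reduction (to 14%), 568 control and 579 insured women, 5% significance (taken as two-sided), 80% power.

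**Inputs assumed, because the protocol gives none.**
- *b*: proportion with a listed symptom from non-STI causes, 5-50%.
- *s*: proportion of STIs that cause a listed symptom, 30-80%.
- *k*: relative cut in non-STI symptoms from insured care, 5-20%.
- The 20% is a cumulative risk. It stands in here for STI prevalence at a visit, which is probably lower.

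**Step 1: the plan's own figure.** Power is Φ((d − 1.96·SE0)/SE1), with SE0 from the pooled and SE1 from the separate proportions; the negligible opposite tail is added in the tables below. For 20% v 14%, the pooled proportion is (568×0.20 + 579×0.14)/1,147 = 0.1697, SE0 = 0.02217 and SE1 = 0.02213. This gives (0.0600 − 0.0435)/0.0221 = 0.75, or 77% power, a little under the stated 80%. It is the benchmark for the test-based measure.

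**Step 2: the planned STI effect seen through the symptom measure.** With STI risk *p*, P(any symptom) = 1 − (1 − b)(1 − p·s). Example with b = 30%, s = 30%: control 1 − 0.70×0.940 = 34.2%, insured 1 − 0.70×0.958 = 32.9%. The difference is 1.3 points and power is 7%. Over the range (difference in points, power):

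| b | s = 30% | s = 50% | s = 80% |
|---|---|---|---|
| 5% | 1.7, 16% | 2.9, 30% | 4.6, 52% |
| 20% | 1.4, 9% | 2.4, 15% | 3.8, 29% |
| 50% | 0.9, 6% | 1.5, 8% | 2.4, 13% |

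Every cell is below 77%.

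**Step 3: STIs unchanged, non-STI symptoms lower in the insured arm.** Keep p = 20% in both arms and replace b by b(1 − k) in the insured arm. Example with b = 30%, s = 30%, k = 20%: 34.2% v 1 − 0.76×0.94 = 28.6%. The difference is 5.6 points, significant in 54% of trials. Rejection rates at s = 30%:

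| b | k = 5% | k = 10% | k = 20% |
|---|---|---|---|
| 5% | 5.2% | 5.8% | 8.2% |
| 20% | 6.6% | 11.6% | 32.8% |
| 50% | 12.5% | 35.6% | 89.1% |

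Higher *s* gives slightly lower rates. Over the whole grid the range is about 5-89%.

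**Step 4: share of control events with no STI-caused symptom.** This is 1 − p·s/P(any symptom). With b = 20-50% and s = 30-50% it is 64-89%. With b = 5% and s = 30-80% it is 21-44%.

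**The case against.** A reader might infer that most symptom events are not STIs, or that the measure is nearly blind to STIs. The protocol does not support either. It gives no symptom rate, no share of STIs that are symptomatic and no share of symptomatic women who are infected, and step 4 shows that the answer turns on the assumed background. Symptomatic women who test negative may also have an STI: trichomoniasis is outside the primary test list, and only two STIs are tested at midline.

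Nor are all eight complaints non-specific. Genital ulcer is among them, and lower abdominal pain is qualified to leave out diarrhoea and menstruation. Section {18a} says that vaginal imbalance may lead to infections, not that they are expected in these women, and it reports that such infections are positively related to STIs and HIV.

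The size of the false signal is equally open. The Discussion warns that care may be under-used, and cover is limited to one hospital and a shared ceiling, so a small cut in non-STI symptoms is plausible. In that case rejection stays close to 5% when background symptoms are rare.

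Finally, the measure is labelled as symptoms and does not enter the test percentages. Section {18a} summarises the primary outcomes as STI acquisition and HIV status, and the sample size rests on any STI. A symptom difference would be seen beside test results.

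All of this stands. It limits how large the problem can be said to be. It does not change the fact that the symptom percentage is listed as a primary outcome without a test and can be moved by the intervention through care for other conditions.

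**Conclusion.** The concern holds as a fault in the choice of one primary measure. Its primary status, the any-one-of-eight rule and the absence of a test requirement are all in the text. The arm difference in free care, the equal treatment of test-positive STIs and the unblinded self-report together make a difference without STI change possible.

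The size is conditional. On the stated assumptions, power for the planned effect is 6-52% against 77% for the test-based measure, and the chance of a significant result with STIs unchanged is about 5-89%. Using the cumulative 20% as prevalence probably flatters the symptom measure, since a lower prevalence at a visit would raise the non-STI share. The test-based STI and HIV measures are unaffected.

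**What to change.** Keep the test-based STI measures and HIV status as the primary outcomes. Move the eight-symptom percentage to the secondary physical-health item, label it 'self-reported genital and pelvic symptoms', and state that it will not be interpreted as STI acquisition.

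Symptoms accompanied by a positive test at the same visit can be reported descriptively. They should not replace the measure as a primary outcome. They are largely a subset of the test outcomes already listed, they drop asymptomatic infections, and they miss STIs outside the midline panel. With background symptoms of 20-50% and 30-50% of STIs symptomatic, their power is about 40-63%, below the 77% for tests alone.

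The change needs no new data, only reclassification and relabelling. There is one fewer primary measure, and symptomatic STIs outside the test panel count only in a secondary outcome. Follow-up was under way at the protocol date and a midline look at the primary outcomes was planned, so the change should be dated and its reason recorded.
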